#### Secondary Outcomes

The secondary outcomes will examine the impact of the 4-week Next4You intervention, compared with a mobile-responsive website on wellness topics, on a range of sexual and reproductive health and well-being outcomes among youth in foster care. Specifically, analyses will assess effects on condom use behaviors, condomless sex, and condom errors; self-efficacy related to sexual consent and communication; attitudes toward condom and contraceptive use; power balance and experiences within sexual relationships; and knowledge of health care rights, educational rights, service locations, and financial literacy. Outcomes will be assessed at 3- and 9-month postintervention follow-ups.

Multimedia Appendix 2 [50-57] highlights our primary and secondary measures, with sample survey items.

### Statistical Methods

#### Overview of Analytical Strategy

Our analysis plan follows a series of analytic steps, including data cleaning, analysis of baseline equivalence and attrition, handling of missing data, descriptive analysis, impact analyses of confirmatory research questions, and exploratory analyses. Throughout the analysis phase, we will use a significance level of 0.05 and employ an ITT framework, whereby young people who were randomly assigned to a condition are considered to be in that condition regardless of engagement level or intervention dosage. All analyses will be carried out using Stata. The results of the power analyses suggest a minimum detectable impact between 0.11 and 0.13, or 11 to 13 percentage points, for the dichotomous outcomes. These figures correspond to a minimum detectable effect size of 0.23 to 0.25 SD, or a reduction in continuous outcome from 50% to 37.5%, assuming a baseline prevalence of 50%.

#### Baseline Equivalence

Prior to estimating any outcome models, the study team will follow WWC group design standards related to baseline equivalence, attrition, and missing data [58]. The team will first test for differences between treatment conditions on baseline measures of all outcomes and demographic factors. Following WWC standards, effect sizes will be computed using Hedge *g* and any differences above 0.05 noted. Because of random assignment, group differences on baseline or demographic factors are unlikely, but baseline measures for all outcomes will be included as a covariate in all planned impact analyses, and any significant differences in demographic factors (ie, effect sizes between 0.05 and 0.25 SD) will be added as additional covariates.

#### Attrition

The team will then calculate overall and differential attrition rates. Overall youth attrition rates will consist of the number of units without observed outcome data in the analysis against the number of units randomized. Differential attrition will be obtained by contrasting the attrition rates between treatment and control groups. Overall youth attrition and differential attrition between the treatment and control groups will be carefully monitored to determine the levels of potential bias.

#### Handling Missing Data

Missing data for all youth who agree to participate in data collection will be addressed with regression imputation using Stata, with special attention paid to WWC recommendations (eg, separately imputing data from treatment and control conditions). Regression imputation is the preferred approach for this study as it can be used to include participants with missing baseline data and missing outcome data (whereas nonresponse weighting, another imputation method, can only be used for the former). The team will use imputation regression models that (1) are conducted separately by condition or include an indicator variable for condition, (2) include all covariates used for adjustment in the impact model, and (3) include the outcome when imputing missing baseline data.

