### Sample Size and Power Analyses

Our proposed sample of 500 young people (with a 1:1 allocation to each condition) would result in the Next4You evaluation being powered to identify effects in the range of small to “substantively important” (ie, 0.25 SDs, in accordance with the WWC standards) [36]. The power analysis estimates were obtained and validated via Optimal Design Plus Empirical Evidence software and the HHS Office of Adolescent Health’s Teen Pregnancy Prevention MDI and MDES calculator. The estimates were developed based on the following parameters in accordance with the funder evaluation standards: simple randomization at the individual level; 25% attrition rate; type I error rate of 5%; type II error rate of 20% (ie, power of 0.80); 2-sided hypothesis test; 50% probability of assignment to the treatment group; outcome prevalence of 50%; 25% of the outcome variance is explained by covariates. The impact model will include the baseline measure of the outcome and age or grade level, sex, and race and ethnicity as covariates consistent with funder requirements. The study team will use a combination of data- and theory-driven approaches to select additional covariates for inclusion in the model to further improve the precision of the impact estimates.

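### Regression imputation is named for missing outcomes with no step that carries imputation uncertainty into the standard errors; read as a single fill-in, the 5% test would run at about 6% to 10%

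*Protocol article*

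**What the plan says.** Handling Missing Data names the method and whom it covers: "Missing data for all youth who agree to participate in data collection will be addressed with regression imputation using Stata". It calls this the preferred approach because it can deal with both missing baseline and missing outcome data. The imputation models must be fitted by arm or carry an arm indicator, must "include all covariates used for adjustment in the impact model", and must use the outcome when a baseline value is imputed. The alternative is set aside on the ground that "nonresponse weighting, another imputation method, can only be used for the former", where the former is missing baseline data.

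Descriptive and Impact Analyses defines the impact sample differently: youth with a baseline survey and at least one of the two follow-up surveys. It chooses the multilevel model partly to keep standard errors from being too small and type I error from rising. The paragraph on multiplicity and sensitivity analyses says those analyses may include a look at missing-data approaches, without naming one. Sample Size and Power Analyses assumes a "25% attrition rate".

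**The concern.** The article describes how missing outcomes are to be predicted, but not how the uncertainty of those predictions reaches the standard error. The only protection described for the standard errors is the site random intercept, which does not address imputation.

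If one value is filled in per missing outcome and then analysed as observed, the model counts more participants than supplied data. When the predictors are the arm and the impact-model covariates, the filled values carry no new information on the treatment effect. With deterministic fill they also sit exactly on the regression line and shrink the residual variance. Confidence intervals would be too narrow and P values too small for the primary and secondary outcomes, and the Benjamini-Hochberg step would start from those P values.

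Two related statements make this worse. The share of imputed outcomes drives the inflation, and the two sections do not agree on who is included. The argument against weighting also removes a valid alternative on a mistaken ground.

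**Working it through.** **Inputs from the article.** N = 500 randomised 1:1, "25% attrition rate" (125 lost, 375 observed), "2-sided hypothesis test" at 5%, power 0.80, prevalence 50%, covariate R² = 0.25 (Sample Size and Power Analyses). The stated minimum detectable effect is 0.23 to 0.25 SD, or 0.11 to 0.13 on the probability scale (Overview of Analytical Strategy).

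**The plan's own figure.** MDES = (1.960 + 0.842) × √[(1 − R²)/(0.25 N)]. With N = 375 and R² = 0.25 this is 2.802 × √(0.75/93.75) = 0.251 SD. Multiplied by √(0.5 × 0.5) it is 0.125. The upper end therefore reproduces on 375 observed outcomes; 0.23 SD needs about 440 to 450.

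**Error rate if imputation is single.** Let m be the share of analysed outcomes that are imputed.

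- Deterministic fill: the reported variance is scaled by (1 − m), while the true variance is scaled by 1/(1 − m). The ratio of reported to true SE is therefore (1 − m).
- One random draw: the reported variance is unscaled and the true variance is scaled by 1/(1 − m) + m. The ratio is 1/√[1/(1 − m) + m].
- Actual type I error = 2 × [1 − Φ(1.96 × ratio)].

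At m = 0.25 the deterministic ratio is 0.75 and the error is 14.2%. The random-draw ratio is 1/√(1.333 + 0.25) = 0.795 and the error is 11.9%.

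| Share imputed (m) | Deterministic | One random draw |
|---|---|---|
| 5% | 6.3% | 6.2% |
| 10% | 7.8% | 7.5% |
| 14% | 9.3% | 8.7% |
| 15% | 9.6% | 8.9% |
| 20% | 11.7% | 10.4% |
| 25% | 14.2% | 11.9% |

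**Simulation check.** There were 6,000 null trials per setting (2,000 for multiple imputation), with a binary outcome, prevalence 50%, R² 0.25, outcomes missing completely at random, imputation by arm from the baseline value, and a single-level linear probability model. Deterministic fill and one random draw gave 14.3% and 11.6% at m = 25%, 9.4% and 8.7% at 14%, 7.7% and 7.5% at 10%, and 6.5% and 6.5% at 5%. Multiple imputation with 20 draws and Rubin's rules gave 5.2%, 4.7%, 4.8% and 4.6% at the same shares. Covariate-adjusted analysis of observed outcomes gave 4.6% to 5.1%.

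**Which share applies.** The article does not give m. Under the impact-sample definition, a 3-month outcome is imputed only for youth who missed 3 months but answered at 9. Taking 25% attrition at 3 months, with 375 observed:

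- m = 5% means 375/0.95 ≈ 395 analysed, so about 20 of the 125 answer at 9 months.
- m = 14% means 62.5/437.5, half of the 125.
- m = 15% means 375/0.85 ≈ 441 analysed, about 66 of the 125.
- m = 25% needs all 125 in the analysis. That requires either the wider population of Handling Missing Data or every one of them answering at 9 months.

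**The weighting sentence.** Nonresponse weighting imputes nothing. It reweights respondents by characteristics known for respondents and nonrespondents alike. The Randomization section places allocation after the baseline survey is submitted, so a randomised youth can miss a whole survey only at follow-up; what may be missing at baseline is single items. Missing follow-up outcomes are therefore where weighting applies, the opposite of what the sentence says.

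**The case against.** The strongest objection is that the article says neither single nor multiple, and never says that filled values are analysed as observed. Multiple imputation is commonly done with regression models. The number of imputations and the combining rule are details that a condensed article may leave to an analysis plan, which is not shown here. The article also commits the team to WWC standards on missing data, whose content cannot be checked here. This stands in part. A reader might infer that the plan fixes single imputation, but the documents do not establish that. What remains is that the article names a method, argues for it and lists its model requirements, and that the ordinary meaning of the named method is one fill-in.

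A reader might also infer that the primary test runs at 14%, almost three times nominal. The documents do not support that as an expected value. It needs deterministic fill for all 125 lost youth in an analysis of 500, while the stated impact sample leaves out anyone with neither follow-up. The 25% is itself a planning assumption.

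A reader might take the use of the outcome when imputing baseline values as a second error. It is at least as consistent with multiple imputation, so it is not counted here.

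The required predictors are a minimum and do not bar using the other wave's outcome, which would add some information; the calculations above use baseline information only. The missing-data sensitivity analysis is optional and would not repair the primary test. The weighting sentence changes no estimate by itself, but it is wrong as written.

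**Conclusion.** The point holds in conditional form. The article names regression imputation for missing outcomes and describes nothing that carries imputation uncertainty into the standard errors. In the ordinary sense of the term, the nominal 5% test would run at about 6% to 10% if 5% to 15% of analysed outcomes are imputed. That share is an assumption; it corresponds to roughly 20 to 66 of 125 youth missed at 3 months answering at 9. The ceiling is about 12% with a random draw and 14% with deterministic fill, at 25% imputed across all 500. The figures rest on R² = 0.25, prevalence 50%, data missing completely at random and imputation from baseline information. If multiple imputation with Rubin's rules is intended, there is no inflation and the fault is one of wording.

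Two parts do not depend on that reading: the sections disagree on who is included, and the reason for rejecting weighting is reversed.

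**What to change.** - Replace regression imputation with multiple imputation by arm, combined with Rubin's rules, with the impact-model covariates and the other wave's outcome in the imputation model. Alternatively, make covariate-adjusted analysis of observed outcomes primary.
- State one population for imputation and analysis, so that Handling Missing Data and Descriptive and Impact Analyses agree.
- Correct the weighting sentence: weighting is not imputation, and it addresses missing follow-up outcomes.
- Make an observed-outcome sensitivity analysis definite rather than optional (redundant if that analysis is made primary).

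The cost is a few sentences and a few lines of Stata. The article places final analyses after follow-up ends, expected by March 2026. Intervals will be wider than under single imputation: at 25% imputed, the true SE is 1/0.75 = 1.33 times what deterministic fill reports. Little is lost against the stated power, since the 0.25 SD figure already reproduces on 375 observed outcomes.

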#### Descriptive and Impact Analyses

The study team will use simple averages and frequency distributions to describe the prevalence of each outcome for youth overall and for the treatment group, by selected demographic characteristics and by usage estimates, to provide an initial understanding of changes in the primary and secondary outcomes before estimating impact estimates using multivariate models. The impact of Next4You will be estimated under the ITT framework by comparing outcomes for individuals assigned to Next4You and those assigned to the control condition. The sample will include all youth who participated in the baseline survey and completed the 3-month follow-up, 9-month follow-up, or both. The study team will model all outcomes with a linear-based 2-level multilevel regression model with youth (level 1) nested within level 2 (sites) to account for the nested structure of the data, adjust for correlated error terms, and avoid underestimating standard errors and increasing the probability of type I errors. The following 2-level random intercept multilevel model will estimate the impacts of Next4You on the primary outcome with separate models estimated for the 3- and 9-month follow-ups:

$$y_{ij}=\;\beta_{o}+\beta_{1}Treat_{1ij}+\beta_{2}Baseline_{2ij}+\beta_{3}X_{3ij}\ldots +\beta_{p}X_{pij}+u_{j}+e_{ij}$$

where $y_{ij}$ refers to the expected probability of exhibiting the corresponding outcome for individual *i* in site *j*; $\beta_{0}$ is the overall mean of the outcome across all groups; $\beta_{1}{Treat}_{1ij}$ is an indicator equal to one for participants assigned to the treatment group and zero for those assigned to the control group; $\beta_{2}{Baseline}_{2ij}$ is the baseline measure of the outcome; $\beta_{3}X_{3ij}+\ldots +\beta_{p}X_{pij}$ represents a vector of individual-level baseline covariates (such as sex, race and ethnicity, and age); $\mu_{j}$ is a site-level random effect; and $\varepsilon_{ij}$ is an individual-level error term. The estimation of the effects of the primary outcome and other dichotomous outcomes via multilevel linear probability models provides a convenient, alternative approach to logit models for interpreting dichotomous outcomes [59]. In particular, linear probability models provide model results on a probability scale that is easier to interpret, whereas logit-based versions of the models express the findings in terms of log odds that are more challenging to interpret.

The use of a 2-level random intercept multilevel model is contingent upon the results of a likelihood-ratio test comparing the fit of the 2-level model against a single-level linear probability model. The null hypothesis for the likelihood-ratio test is that there is no significant difference between the two models. A *P* value of <.05 for the likelihood ratio test would result in the rejection of the null hypothesis, as there was a statistically significant difference between the models with the 2-level model fitting significantly better than the single-level linear probability model. In the event that the null hypothesis could not be rejected, the study team will use a single-level model.

The team will adjust *P* values to account for multiple hypothesis testing within each primary and secondary outcome domain using the Benjamini-Hochberg procedure [60]. Finally, the study team will conduct sensitivity analyses to test the robustness of the findings to alternative assumptions or specification of the multilevel models. Sensitivity analyses may involve comparing findings between multilevel logistic regression and multilevel linear probability models, assessing the sensitivity of approaches for addressing missing data, and assessing the impact of sibling participation on outcomes.

#### Implementation Data Analyses

User analytics captured directly on the platform will be analyzed to monitor participant engagement with both the intervention and comparison group platforms, exploring user profiles and how engagement may relate to behavioral outcomes in our analyses. Specifically, the study team will use these data to conduct exploratory analyses of dosage and treatment effects as moderators to assess how, if at all, the level of exposure to the platform influences the strength of the observed intervention effect. These data will also be within sensitivity analyses where a “treatment on the treated” analysis framework is used to examine the robustness of the impact estimates under the ITT framework. Various definitions of intervention uptake will be examined, including amount, frequency, duration, and depth among participants who ultimately received the condition to which they were assigned (ie, “compliers”). The effect of treatment receipt for the subgroup of compliers, or the local average treatment effect, will be estimated using instrumental variable methods with a two-stage least squares estimator. In the two-stage least squares, the first stage will involve using the random assignment indicator to predict intervention participation, and the second stage will use the predicted values of intervention participation from the first stage intervention to estimate intervention effectiveness.

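### The treatment-on-the-treated analysis is a rescaled ITT result, so it cannot test the robustness of ITT; its definition of compliers and its use of dose as a moderator also need correcting

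*Protocol article*

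**What the plan says.** All of this is in the protocol article, mainly under Implementation Data Analyses.

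- **Role.** The treatment-on-the-treated "analysis framework is used to examine the robustness of the impact estimates under the ITT framework". It is placed among the sensitivity analyses.
- **Uptake.** "Various definitions of intervention uptake will be examined, including amount, frequency, duration, and depth". Implementation Evaluation Data Collection puts these four metrics on count, time or percentage scales. Neither section states a cut-off.
- **Compliers.** They are described as "participants who ultimately received the condition to which they were assigned".
- **Estimator.** The local average treatment effect "will be estimated using instrumental variable methods with a two-stage least squares estimator", where "the first stage will involve using the random assignment indicator to predict intervention participation". No other instrument is named.
- **Dose.** The platform data will also be used to "conduct exploratory analyses of dosage and treatment effects as moderators", to see whether exposure changes the strength of the effect.

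Two statements elsewhere matter. Comparison Intervention gives the comparison group the Next4You site only once its 9-month evaluation period is over. Overview of Analytical Strategy makes ITT the framework for the analysis.

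**The concern.** A sensitivity analysis is informative only if it could give a different answer from the main analysis. The 2SLS estimate described here practically cannot, because it is computed from the ITT effect. If it is reported as a robustness check, four uptake definitions would look like four confirmations when they are nearly one test repeated.

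The description of compliers raises a separate problem. Compliers are a latent group: youth who would use Next4You if assigned to it and would not otherwise. Observed receipt of the assigned condition is something else. If the sample were limited on that basis, the comparison would no longer be between randomised groups.

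The dose analysis has a similar weakness. Platform use arises after randomisation and is chosen by the participant. Strengths and Limitations itself says that a self-paced programme depends on motivation and engagement. A relation between dose and outcome could then be reported as dose-response when it reflects who chose to engage.

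**Working it through.** **1. The plan's own figure, used below as an illustrative ITT effect.** Inputs from Sample Size and Power Analyses: N = 500, 1:1 allocation, 25% attrition, two-sided alpha 0.05, power 0.80, prevalence 50%, 25% of variance explained by covariates.

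- Analysed N = 500 × 0.75 = 375.
- Minimum detectable effect size = (1.960 + 0.842) × √[(1 − 0.25)/(0.25 × 375)] = 2.802 × 0.0894 = 0.251 SD.
- Minimum detectable impact = 0.251 × 0.5 = 0.125.

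This agrees with the stated ranges of 0.23 to 0.25 SD and 11 to 13 percentage points. The article gives no figure for the 2SLS analysis.

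**2. What 2SLS returns.** Let π be the arm difference in uptake. With one binary instrument and one uptake variable:

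- Estimate = ITT / π.
- Its standard error also carries the factor 1/π, so π cancels from the z-statistic. What remains is a small difference in residual variance.

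The article gives no uptake rate, so a range is assumed. With ITT = 0.125:

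| Assumed uptake difference π | 0.125 / π |
|---|---|
| 0.95 | 0.132 |
| 0.80 | 0.156 |
| 0.60 | 0.208 |
| 0.40 | 0.312 |
| 0.30 | 0.417 |

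**3. Simulation of the agreement.** Settings: 375 youth, 4,000 runs, no covariates, no Next4You use in the comparison arm. Assumed use in the Next4You arm: 15% no lessons, 25% all 50, the rest spread evenly between. The effect was linear in lessons, with mean lessons 0.25 × 50 + 0.60 × 25 = 27.5 and effect per lesson 0.125 / 27.5 = 0.00455.

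| Uptake defined as | Uptake | Mean ITT | Mean 2SLS | True mean effect in that group | Correlation of z-statistics |
|---|---|---|---|---|---|
| ≥1 lesson | 0.85 | 0.125 | 0.147 | 0.147 | 0.9999 |
| ≥15 | 0.68 | 0.125 | 0.184 | 0.176 | 0.9998 |
| ≥25 | 0.56 | 0.125 | 0.225 | 0.195 | 0.9996 |
| ≥40 | 0.37 | 0.125 | 0.336 | 0.219 | 0.9988 |
| 50 | 0.25 | 0.125 | 0.505 | 0.227 | 0.9964 |

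- At every cut-off the two estimates had the same sign in all runs. The verdict at 0.05 differed in at most 0.4% of runs.
- At any use, the 2SLS estimate equals the true effect in users. At higher cut-offs it exceeds that effect, because youth below the cut-off also benefited and the exclusion restriction fails.
- With lessons as a continuous treatment, 2SLS gave 0.00454 per lesson against a true 0.00455, so there was no inflation. The verdict at 0.05 differed from ITT in about 0.1% of runs.

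**4. The complier description against the access rule.** Comparison youth cannot reach Next4You during the evaluation period, so essentially all of them count as having received their assigned condition. In the Next4You arm, only users do. Under the assumed 85% uptake, 15% of the 187 comparison youth, about 28, would never have used Next4You but would still be counted. Their counterparts in the Next4You arm would not. An analysis limited to this group therefore compares users with a mixture of would-be users and would-be non-users.

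**5. Dose as a moderator.** A moderator of a randomised effect has to be fixed before randomisation or be unaffected by it. Next4You dose is neither, and it has no counterpart in the comparison arm, whose platform offers different content.

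**The case against.** The strongest reply is that the analysis is better specified than the criticism implies. The section names the estimand, the estimator and the instrument, and these define a complier effect whatever the parenthetical says. It nowhere states that the 2SLS sample is restricted. With binary uptake, restricting it would make assignment and participation identical and leave the first stage nothing to estimate. The dose work is labelled exploratory. The confirmatory analysis is ITT, and a condensed article may leave the choice of uptake definition to the analysis plan.

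Much of this stands. A reader might infer that the plan applies a series of rising uptake thresholds and so inflates the effect. The article does not support that: it lists four metrics and no cut-off, and a continuous coding is open. Nor is a 2SLS estimate larger than ITT inflation in itself. At any use, with no access in the comparison arm, it is a valid complier effect under the exclusion restriction. A reader might also infer that a per-protocol analysis is planned; the wording leaves that open but does not say it. An objection to pooling raw lesson and pamphlet counts would go too far as well, since pooling is not stated and depth is a percentage of available content.

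The reply does not rescue three things the text states: the role as a robustness check, the description of compliers, and dose as a moderator. The exploratory label does not change what a moderation analysis on a self-selected variable estimates.

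**Conclusion.** The concern holds in a limited form. As described, the 2SLS analysis answers a different question from ITT and practically cannot disagree with it, so it should not be offered as evidence of robustness, whether once or over four metrics. The description of compliers is wrong and leaves the analysis sample unclear. Dose relations cannot be read as moderation of the randomised effect.

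The identity ITT / π is exact when both analyses use the same sample and covariates in a single-level linear model; with a site random effect in the ITT model it is approximate. The sizes shown rest on an assumed ITT effect of 0.125, assumed uptake of 30% to 95%, and an assumed lesson distribution with a linear effect. Bias at higher cut-offs is conditional on uptake being dichotomised above any use and on use below the cut-off affecting outcomes.

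The primary ITT analysis, the significance level and the sample size are unaffected. What is at stake is what the trial may claim from its secondary and exploratory results.

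**What to change.** 1. Present the 2SLS result as a supplementary estimand, the effect in compliers, and remove it from the sensitivity analyses of ITT. The other sensitivity analyses listed under Descriptive and Impact Analyses (logistic against linear models, missing-data approaches, sibling participation) can genuinely disagree with the main result and should carry that role.
2. Define compliers as youth who would use Next4You if and only if assigned to it.
3. State that 2SLS is run on all randomised youth in the analysis sample, with no selection on receipt.
4. Fix one main uptake definition before outcomes are seen: either any Next4You lesson opened, or lessons completed as a continuous treatment with the linearity assumption stated. Other definitions may be shown as secondary, with a note that they repeat nearly the same test.
5. Report relations between engagement and outcome within the Next4You arm as descriptive associations, not as moderation of the randomised effect.

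The cost is a change of wording. Fewer uptake definitions carry weight, and no causal dose-response claim can be made. No data collection and no confirmatory analysis changes.
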